### Data Analysis Plan

Preliminary analyses exploring the data set will be conducted, including descriptive statistics and exploratory graphing for all the variables of interest measured during the study, which will allow for the identification of outliers (eg, measurements or recording errors and logical inconsistencies in data). The key baseline variables (eg, sex) will be considered as plausible covariates in the planned analyses.

#### Primary Outcome Analysis

##### Effects of the Intervention on the Proximal Outcomes

The weighted and centered least squares method developed by Boruvka et al [105] to evaluate data from MRT studies will be used to estimate and test the causal excursion effects of the intervention on the proximal outcomes. This method assesses parameters in treatment effect models and allows for the inclusion of covariates that can reduce the variance of the treatment effect estimates. Similar to generalized estimating equations and multilevel models, this method can effectively manage nested data (ie, decision points nested within participants) and within-person dependencies across time in the outcome. A detailed explanation of the analyses is available in Multimedia Appendix 4 [23,51,105,106].

As a primary goal of this study, we will test the overall (average, across all decision points) effect of engaging in any intervention versus engaging in the control intervention on the emotional states measured with the postintervention EMA upon intervention completion. Furthermore, we aim to evaluate whether this effect deteriorates over time by estimating the interaction between the overall intervention effect and the day in the study.

As a subgoal, we will examine differences in the overall effect of engaging in a suggested intervention versus engaging in the control intervention on emotional states for each intervention category separately. We will control for the pretreatment scores of positive and negative affect measured by the preintervention EMA across all models. To account for repeated dependent measures, robust SEs will be calculated using a sandwich estimator, and because we are comparing multiple outcomes, the results will be controlled for multiple testing using Bonferroni correction, that is, we will divide the α value by the number of comparisons being made (ie, 2; hence, we will use α=.025).

Data may be missing if participants do not complete the EMAs before and after an exercise because without the completion of both measurements the observation for the proximal outcome will be missing. If no more than 10% of the data are missing, our primary analysis will be performed as a complete case analysis. If >10% of data are missing, the missing data will be handled by using multiple imputation approaches and outcome models averaged across imputations to adhere to the intention-to-treat principle.

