### Participants

#### Phase 1: MRT

##### Overview

A total of 200 students at EUR will be recruited. A web-based sample size calculator for MRT studies [57,58] was used to calculate the sample size based on the duration of the intervention period (21 days), expected availability intervention randomization probability (60%), and proximal treatment effect. We expect that participants will respond to approximately 70% of the prompts throughout the intervention period (ie, we assume a constant availability of 70%). Furthermore, we assume a linear effect of the intervention on the proximal outcome measures over time with an average size of 0.1 and an initial effect of 0 at the start of the study. In comparison with the large effect size for in-person therapy based on transdiagnostic approaches to emotional disorders [59], we assume a smaller effect size for our study, which is in line with the results of internet interventions for MH in university students [27] and with a similar MRT study protocol examining an ACT intervention [54]. On the basis of these assumptions, 126 participants will generate 80% power to detect the assumed effect with a significance level of .05. We will increase the participant number to 200 to account for a dropout rate of 40%, in line with average attrition rates for MH interventions delivered through smartphones [60].

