Every time participants fill in the preintervention EMA, they have a 60% chance of receiving an exercise and a 40% chance of receiving a health snippet. The 60:40 ratio was chosen to ensure a higher chance of receiving an intervention at every decision point. This strategy has been used in previous MRT studies too [51,52]. For this study, a simple randomization with replacement will be used. The randomization is carried out automatically within the app and is as follows:  randomization of exercise (60% chance) or control intervention; if an exercise is chosen, a second randomization to the intervention categories follows (20% chance for each intervention category), followed by the random selection of 1 exercise within the randomized intervention category (equal chance across exercises); if a control intervention is randomized (40% chance), a second randomization takes place in which a health information snippet is selected. Participants will be asked to complete 42 preintervention EMAs and 42 postintervention EMAs in total during the study. They can receive an exercise 0 times, 1 time, or maximally 2 times in a day. On average, they will be prompted to engage in 1.2 exercises per day and 25.2 exercises throughout the study.

Upon the completion of either the exercise or the control intervention, the participants are asked to reassess their emotional state by completing the postintervention EMA. When assigned to an exercise, in addition to the postintervention EMA, participants will be asked to rate the likability and helpfulness of the exercise. When CD exercises are selected, participants will also complete the corresponding measures of thought believability and discomfort before and after the exercise.

Given that the primary objective of this study is to evaluate the functioning of the intervention rather than observe it in a naturalistic setting, we have implemented an adherence protocol to enhance completion rates and ensure high-quality data. To support participants in staying engaged, they will receive emails or telephone calls from researchers, depending on the number of missed sessions. The adherence protocol is presented in Multimedia Appendix 3.

Immediately after the intervention period is concluded, participants will complete the postintervention assessment, including the secondary outcome measures (refer to Table 1 for an overview of the measurements performed during phase 1 of the study).

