Compared with other methodologies used for intervention evaluation such as an RCT, the MRT design makes it possible to observe proximal changes in participants’ emotional states directly after they complete an exercise, in addition to requiring fewer participants to achieve sufficient power to detect the proximal main effect of an intervention component [52]. This enables insight into the mechanisms of change (ie, changes in emotional states), elucidating on how the intervention and its components stimulate the desired benefits (ie, increase in ER skills and decrease in depressive and anxiety symptoms). Combining results from the MRT with information on user engagement patterns (ie, log data analytics) and user experience (ie, exercise ratings and user experience interviews) will help unpack the black box typical of studies of digital MH interventions, where often little is known about the mechanisms by which the interventions exert their benefit [109]. The combined results will also indicate intervention components that might need improvements or should be discarded when they play no significant, or possibly impeding, role in facilitating the desired change. This means that if an intervention category is perceived as unhelpful, unlikable, or unclear or was hardly used by participants, and when it was used, it showed a negative or no effect on proximal outcomes, the intervention category (or specific exercises) could be removed from the intervention library or redesigned. Furthermore, the use of a mixed methods approach not only offers the opportunity to gather valuable insight into how the current generation of students perceive and engage with digital MH interventions but also sheds light on how they receive the MRT as a method of evaluation. This information can help optimize future endeavors in the development and evaluation of tools for digital MH interventions. Finally, the results of exploratory analyses and the data set obtained in this study will be used to develop and train the recommendation algorithm, maximizing the likability and usefulness of exercises for users based on individual (ie, personality and MH status) and contextual (eg, the time of day and momentary emotional states) characteristics. Creating a system that can suggest content relevant to its users has been indicated as a top priority for university students to engage and remain engaged in an MH app [18]. Therefore, designing and implementing a recommendation system in the app may be crucial in improving its uptake and effectiveness.

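### The analysis plan sets each exercise category only against the health snippet and names no comparison between categories, although a non-significant category may count toward removal or redesign

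*Protocol article*

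**What the plan says.** Under Effects of the Intervention on the Proximal Outcomes, the primary test pools all exercises against the snippet. A subgoal then looks at the effect "versus engaging in the control intervention on emotional states for each intervention category separately". The significance level is halved for the two affect outcomes ("hence, we will use α=.025").

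The Study Objectives ask whether the intervention and its separate categories have their intended effects, and define this as exercise compared with control. The exploratory objective lists intervention type among the moderators. The section on contextual moderators in the analysis plan names time of delivery, momentary emotional state, GHQ-12 score, personality and gender, but not intervention type. Categories appear there only as effects to be moderated.

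The Discussion (Overview) says that the combined results will point to "intervention components that might need improvements or should be discarded when they play no significant, or possibly impeding, role in facilitating the desired change". It then explains that a category could be removed or redesigned if it is poorly perceived or hardly used and also shows a negative or no effect on the proximal outcomes.

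**The concern.** The snippet contrasts answer whether each category works. They do not answer whether one category works better than another. If one contrast is significant and its neighbour is not, that is not evidence that the two differ: the gap between them may be well within sampling error.

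The results are meant to feed redesign decisions and the first rules of a recommendation algorithm, and both involve choosing among categories. With low power per category, a mixed set of verdicts is likely even when the categories are equally effective. An effective category could then have non-significance counted against it, although the trial randomises the categories and could compare them directly.

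**Working it through.** **The plan's own figure.** The sample size section states that "126 participants will generate 80% power to detect the assumed effect with a significance level of .05", for an effect "with an average size of 0.1 and an initial effect of 0 at the start of the study". I used a two-parameter test (intercept and day) with 42 decision points, availability 0.7 and randomisation variance 0.6 × 0.4. The noncentrality at N = 126 is 12.15. This gives 80% power at N = 104 with alpha .05 and at N = 123 with alpha .025. At N = 126, power is 0.88 and 0.81 respectively. So 126 is reproduced to within three participants at the alpha used in the analysis, but not at the alpha printed beside it. The calculator's settings are not shown, and the point below does not depend on this. The figure concerns the pooled effect; no category-level power is given.

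**Inputs for the category contrasts.**
- Decision points: 42 per participant ("Participants will be asked to complete 42 preintervention EMAs and 42 postintervention EMAs in total during the study").
- Response: 70% (sample size section).
- Allocation: snippet 40%; each category 20% of 60% = 12% (Phase 1 procedure).
- True effect: 0.1 SD in every category. The protocol assumes 0.1 for the overall effect; applying it to each category is my assumption.
- Two-sided alpha .025, critical value 2.241.
- Assumed: SD 1, independent residuals, effect constant at its average.

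**Power per category.** SE = √(1/n_cat + 1/n_snippet); power = Φ(0.1/SE − 2.241).

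| N | Flows (N × 42 × 0.7) | Per category | Snippet | SE | 0.1/SE | Power |
|---|---|---|---|---|---|---|
| 126 | 3,704 | 445 | 1,482 | 0.054 | 1.85 | 0.35 |
| 137 | 4,028 | 483 | 1,611 | 0.052 | 1.93 | 0.38 |
| 161 | 4,733 | 568 | 1,893 | 0.048 | 2.09 | 0.44 |

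**Chance of a split verdict.** I simulated 400,000 trials with five equal effects of 0.1 and a shared snippet arm, and counted trials with one to four of the five categories significant on one affect outcome.

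| N | None significant | All five | Split |
|---|---|---|---|
| 126 | 0.20 | 0.03 | 0.77 |
| 137 | 0.18 | 0.03 | 0.79 |
| 161 | 0.12 | 0.06 | 0.82 |

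**Dependence on the common effect (N = 126).**

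| Common effect (SD) | 0.05 | 0.08 | 0.10 | 0.12 | 0.15 | 0.20 | 0.25 |
|---|---|---|---|---|---|---|---|
| Split | 0.34 | 0.62 | 0.77 | 0.83 | 0.72 | 0.28 | 0.04 |

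**Chance spread.** With equal true effects, the best and worst observed categories differ on average by 0.11 SD at N = 126 and 0.10 SD at N = 161, about as much as the assumed effect itself.

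**The direct comparison.** With equal effects, a 4-df equality test at .025 rejects in 2.5% of trials. Its power at N = 137 comes from a noncentral chi-square with noncentrality 483 × Σ(effect − mean)² and critical value 11.14:
- one category null, four at 0.1: 483 × 0.008 = 3.87, power 0.22;
- one category null, four at 0.2: 483 × 0.032 = 15.5, power 0.84;
- effects spread evenly from 0 to 0.2: 483 × 0.025 = 12.1, power 0.72.

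**The case against.** The planned contrasts match the stated objective, which asks whether each category has its intended effect against control. That stands, and they should be kept.

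A reader might infer that categories will never be compared. The documents do not support this. Intervention type is listed as an exploratory moderator, the wording of the subgoal on differences is ambiguous, and the analytic detail is in Multimedia Appendix 4, which is not shown. What can be said is that the analysis section specifies no such comparison.

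A reader might also infer that P values alone decide which categories survive. They do not. The Discussion combines effect with perception or use, draws on the interviews, and describes removal only as a possibility. It states no rule for keeping a category. Still, the effect on affect is its only efficacy input, and it is worded in terms of significance.

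Finally, a split verdict among truly effective categories is a failure to detect effects against control, not a false claim of difference. The 77% and the 2.5% are therefore error rates for different questions. That is right. The split rate shows how little a mixed pattern says about differences; the equality test does not cure the low power.

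**Conclusion.** The point holds in limited form. The analysis section names only snippet contrasts by category, while the Discussion lets non-significance contribute to removing or redesigning one. At the protocol's planning effect, applied to every category, each contrast has about 35% to 44% power, and about 77% to 82% of trials would give a mixed pattern on a given affect outcome with no true difference between categories.

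It would be tempting to say that about eight in ten such trials would sort equal categories wrongly, whatever the truth. The figure does not carry that: it applies near a common effect of 0.1 and is about 34% at 0.05 and 28% at 0.20. It also rests on SD 1, independent residuals and 70% response. This is a change that should be made; it does not invalidate the primary analysis.

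**What to change.** Keep the category-versus-snippet contrasts as the answer to the stated objective, and make these changes:
1. Estimate all five in one weighted and centered model with a shared snippet control (probabilities .12 for each category and .40 for the snippet).
2. For each affect outcome, add a 4-df Wald test of equal category effects at .025.
3. Report the five estimates with confidence intervals, optionally with partially pooled estimates beside them.
4. State that categories differ only on the basis of the between-category comparison.
5. In the Discussion, replace the reference to a non-significant role with a reading of the estimate and its interval. For scale, at N = 126 a 95% interval for one category extends about 1.96 × 0.054 = 0.106 SD either side, so an estimate of 0.05 would be compatible with both zero and the planned 0.1.

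The cost is one model and a few sentences, with no new data. The article reports that data collection is complete and analysis under way, so the change should be recorded before category results are examined. The downside is low power for small differences (about 22% at N = 137 with one null category and four at 0.1). Non-rejection must not be read as equality, and the equality test should not decide whether a category may be judged ineffective against the snippet.

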##### Thought Believability and Discomfort Outcome

A multiple linear regression model will be applied to assess the effects of CD exercises on the level of thought believability and discomfort measured before and after CD exercise completion.

#### Feasibility Outcomes

##### Objective Engagement Patterns

Descriptive statistics of engagement metrics (ie, completion rate, average time spent, and the time of day when participants completed the exercises) per exercise and exercise categories will be examined to evaluate exercise performance and inform further design revisions. A linear mixed model will be used to analyze whether there is a relationship between the time of day and exercise completion rates.

##### Subjective Engagement Patterns

To gain insights into subjective engagement with the exercises, we will combine information on (1) the exercise likability and helpfulness ratings and (2) semistructured interviews with a subset of participants purposefully recruited based on their adherence levels (refer to the *Participants* subsection).

##### Exercise Likability and Helpfulness

For every exercise, average scores on likability and helpfulness scales are computed across all participants, with higher scores indicating higher levels of likability and helpfulness of the exercise. Exercises will then be ranked from the most liked and helpful to the least, informing on which exercises may be perceived as difficult by participants and pointing to potential design revisions of exercise content or user experience design.

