##### Intervention Engagement

Objective engagement parameters are retrieved from app use analytics (ie, log data) and consist of exercise completion rate, average time spent per exercise, and the times when participants most frequently engaged in an exercise (morning or evening). Subjective engagement parameters of exercise likability (“How much did you like the exercise?”) and helpfulness (“How helpful did you find the exercise?”) scores measured on a scale ranging from 1 (not at all) to 100 (very much) are assessed at the conclusion of each exercise.

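### The 20 exercises are ranked on raw mean ratings despite up to 2:1 unequal expected rating counts and no adjustment for rater, so the ranking is noisier than it need be

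*Protocol article*

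**What the plan says.** Likability and helpfulness are listed among the primary outcomes, under Intervention Engagement, as "scores measured on a scale ranging from 1 (not at all) to 100 (very much) are assessed at the conclusion of each exercise". Under Feasibility Outcomes, the section Exercise Likability and Helpfulness fixes the summary: "For every exercise, average scores on likability and helpfulness scales are computed across all participants". It continues: "Exercises will then be ranked from the most liked and helpful to the least". The stated purpose includes "pointing to potential design revisions of exercise content or user experience design". The section mentions no adjustment for rater, no interval and no allowance for the number of ratings.

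The exposure of each exercise is set in Study Procedure, Phase 1: MRT. At each completed preintervention EMA, "they have a 60% chance of receiving an exercise and a 40% chance of receiving a health snippet". Given an exercise, each of the 5 categories has a 20% chance, and one exercise is then drawn with equal chance within the category. Draws are made with replacement. The textbox of exercises lists 3 for positive affect, 4 for mindfulness, 6 for cognitive defusion, 4 for relaxation and breathing, and 3 for self-compassion.

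Three other places bear on how the ranking is used:
- Objective Engagement Patterns already plans completion rates per exercise.
- Subjective Engagement Patterns combines the ratings with interviews.
- The Discussion overview says that, under a joint condition that includes a negative or null proximal effect, "the intervention category (or specific exercises) could be removed from the intervention library or redesigned".

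**The concern.** Equal chances per category with unequal category sizes mean unequal chances per exercise. A ranking of raw means treats an average from few ratings as being as firm as one from twice as many, and the less precise averages tend to land at both ends of the list.

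The raw mean also mixes two things: how the exercise is liked, and how generously the participants who drew it use the 1-100 scale. With independent draws and only about one draw per participant per exercise, different exercises are rated by different sets of people. Random assignment stops this from biasing the means, but it stays in them as noise, although the design allows each participant to serve as their own reference.

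At stake is which exercises are picked out for redesign. An exercise could be singled out because it was rated seldom or by strict raters, and not because of its content.

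**Working it through.** **The plan's own figure.** 2 × 0.60 = 1.2 exercises per day and 42 × 0.60 = 25.2 in the study. Both match the article.

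**Expected exposure per exercise.** For a category of k exercises, the chance per flow is 0.60 × 0.20 / k. Assignments per participant are 42 times this. Expected ratings are that number × 0.70 × N. The 0.70 is the availability in the sample size section. N is 137 (completed phase 1) or 200 (planned).

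| Category size k | Exercises | Chance per flow | Assignments per participant | Ratings, N=137 | Ratings, N=200 |
|---|---|---|---|---|---|
| 3 | 6 | 4% | 1.68 | 161 | 235 |
| 4 | 8 | 3% | 1.26 | 121 | 176 |
| 6 (defusion) | 6 | 2% | 0.84 | 81 | 118 |

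Check: 6 × 4% + 8 × 3% + 6 × 2% = 60%. With equal completion and equal rating variance, the standard error of a defusion mean is √(4/2) = 1.41 times that of an exercise in a 3-exercise category, and √(3/2) = 1.22 times that of one in a 4-exercise category.

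**Share of noise due to raters.** The article gives no rating standard deviations, so three pairs (between raters, residual) were assumed. The rater share of the variance of a single rating is:
- (10, 20): 100/500 = 20%
- (15, 20): 225/625 = 36%
- (20, 15): 400/625 = 64%

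**Effect on the ranking.** The randomization was simulated 1,500 times per setting, with availability varying between participants around a mean of 0.70. The true standard deviation between exercises was set to 0, 2, 5 or 8 points. The fair share of last places for the 6 defusion exercises is 6/20 = 30%, and simulation error on a proportion near 30% is about √(0.3 × 0.7/1500) = 1.2 percentage points. Results for N=137:

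| Raters, residual SD | True SD between exercises | Defusion last: raw | Defusion last: adjusted for participant | Defusion last: shrunken | Rank correlation with truth: raw | Adjusted | Shrunken |
|---|---|---|---|---|---|---|---|
| 15, 20 | 0 | 46% | 47% | – | – | – | – |
| 15, 20 | 2 | 40% | 38% | 23% | 0.61 | 0.67 | 0.68 |
| 15, 20 | 5 | 34% | 33% | 29% | 0.87 | 0.90 | 0.91 |
| 15, 20 | 8 | 30% | 30% | 27% | 0.94 | 0.95 | 0.95 |
| 20, 15 | 2 | 40% | 35% | 25% | 0.62 | 0.77 | 0.77 |
| 20, 15 | 5 | 33% | 31% | 28% | 0.87 | 0.94 | 0.94 |

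Over all assumed pairs and both sample sizes, the raw ranking puts a defusion exercise last in 45-47% of runs at true SD 0, 37-41% at 2, 32-34% at 5 and 29-32% at 8. By symmetry of the simulated distributions, the same holds for first place.

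**Reading.** There are two separate effects. Adjusting for participant improves the order at every non-zero spread tried, but leaves most of the excess of defusion exercises at the extremes, since that comes from unequal counts. Shrinkage removes the excess but takes defusion exercises below their fair share, and adds almost nothing to the rank correlation.

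**The case against.** The strongest reply is that this is descriptive feasibility work with no test and no claim of superiority, that counts and intervals are details a condensed article may leave to a fuller plan, and that the ranking is only one input. Much of this stands, and it rules out several stronger readings.

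- A reader might infer that the ranking alone removes exercises. The Discussion overview does not support that: poor perception or low use must coincide with a negative or null proximal effect, and even then removal or redesign is only a possibility. Interviews are added as well. The safeguard is weaker for single exercises, because the primary analysis describes proximal effects overall and by category only.
- A reader might infer that abandoned exercises go unnoticed, because ratings "are assessed at the conclusion of each exercise". Selective completion could indeed bias a mean, but completion rates per exercise are already planned.
- A reader might infer that strict raters bias the means. Under within-participant randomization they add noise, not bias.
- A reader might infer that frequent users weigh more. The text does not say whether single ratings or participant means are averaged.

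At category level the 2:1 imbalance disappears, since every category has the same 20% chance. What the reply does not meet is that the article names a specific statistic and ranks single exercises on it, when a more precise one is available from the same data.

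**Conclusion.** The point holds as a modest loss of precision in a stated method. The 2:1 ratio of expected counts and the 1.41 ratio of standard errors follow from the article's own probabilities, given equal completion and similar rating variance across exercises. The avoidable rater noise follows from the design. Its size depends on assumed standard deviations: at N=137 and a true spread of 2 points, adjustment raises the rank correlation from 0.61 to 0.67 or, with larger rater differences, from 0.62 to 0.77. At 5 points the gain is 0.87 to 0.90 or 0.94.

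It would be too strong to say that the plan pushes defusion exercises to the extremes without qualification. The figure of 45-47% last places applies only if all 20 exercises are truly equal. The excess matters when true differences are about 0 to 3 points, is small at 5 and is negligible at 8. The article gives nothing that shows which case applies.

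**What to change.** Base the ranking on exercise means adjusted for participant, from a linear mixed model of each rating with exercise effects and a random participant effect. In one table, give each adjusted mean with its interval and number of ratings, and beside it the completion rate per exercise already planned under Objective Engagement Patterns. The interval and the count make the unequal precision visible, which the adjustment alone does not cure. Raw means can stay as a further column.

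Shrunken exercise effects may be added as a sensitivity view only, because shrinkage makes exercises with few ratings less likely to be flagged and could hide a defusion exercise that is genuinely disliked.

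The cost is one extra model on data already collected and a ranking that is slightly harder to explain. The article reports that analyses were still under way and already plans a linear mixed model for completion rates, so the change is a small one.
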